## Exclusion period and participation in other research

There is no exclusion period during which participants are prohibited from enrolling in another study. However, participants must not take part in any other study that could interfere with the primary objective of the MUSIBOT study.

## Volunteer compensation

Participants will not receive any financial compensation.

## Recruitment methods

Patients requiring botulinum toxin injections will be recruited during Physical Medicine and Rehabilitation (PMR) consultations in a hospital setting. In addition to requiring treatment with botulinum toxin, patients must meet the inclusion and exclusion criteria described above to be eligible for the study.

Information about the study will be provided during the prior consultation (at least one month before the injection). Patients will be given a reflection period of no less than 1 month and no more than 3 months to decide whether to participate. They may contact the secretary of the referring physician who performs the botulinum toxin injections or the Clinical Research Associate (CRA) of the department to communicate their decision.

The inclusion of legally protected adult patients in this clinical trial is essential to ensure the representativeness of our target population, which includes individuals with stroke, traumatic brain injury, multiple sclerosis, or cerebral palsy. These conditions frequently lead to the implementation of legal protective measures, and excluding such individuals would introduce a significant bias and limit the generalizability of our findings. Moreover, this trial aims to optimize the use of botulinum toxin, a common treatment for these patients. The potential benefits, such as improved injection protocols and more personalized care, fully justify their inclusion.

We are committed to strictly adhering to the ethical and legal principles governing research involving vulnerable persons. Informed consent will be obtained from legal guardians or representatives, while actively involving patients in the decision-making process according to their abilities.

# STUDY METHODOLOGY

## Evaluation criteria

### Primary endpoint

Patient stress, assessed during Injection Visit #1, will be estimated by changes in Heart Rate Variability (HRV), measured before and during the botulinum toxin injection session using the LF/HF ratio.

The LF/HF ratio is a reliable indicator of the balance between sympathetic and parasympathetic nervous system activity. It provides insight into stress regulation, cardiovascular health, and physiological adaptation. A lower LF/HF ratio may be associated with improved recovery, better emotional regulation, and a healthier autonomic nervous system balance.

HRV will be measured using a Polar H10 heart rate monitor belt. Data will be exported to the Elite HRV application and analyzed using KUBIOS software.

### Secondary endpoints

- Patient stress during Injection Visit #2, estimated by changes in HRV, measured before and during the botulinum toxin injection session using the LF/HF ratio.
- Pain intensity experienced by the patient during Injection Visits #1 and #2, measured immediately after the injection session using a simple Numerical Rating Scale (NRS) ranging from 0 (“no pain”) to 10 (“worst imaginable pain”).
- Anxiety variation measured by the self-administered State-Trait Anxiety Inventory - Form Y, State subscale (STAI-Y1) during Injection Visits #1 and #2, before and after the botulinum toxin injections. The STAI-Y1 consists of 20 items rated on a 4-point Likert scale, from 1 (“Not at all”) to 4 (“Very much”) (see ANNEX 2).
- Patient’s perception of the duration of the session relative to the actual injection time during Injection Visits #1 and #2. This self-reported data will be collected at the end of each session.
- Patient satisfaction with the intervention assessed using a Visual Analog Scale (VAS) ranging from 0 (“no satisfaction”) to 10 (“highest satisfaction”), measured after the injections during Visits #1 and #2.
- Quality of the botulinum toxin injection conditions, as assessed by the physician immediately after each session during Visits #1 and #2, using a simple Numerical Rating Scale (NRS) from 0 (“extremely poor conditions”) to 10 (“extremely good conditions”).

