## Secondary objectives

To evaluate the effect of exposure to a musical intervention session during botulinum toxin injections at Injection Visit 1 on:

- - Injection-induced stress as assessed by HRV parameters excluding the LF/HF ratio
  - Injection-induced pain
  - Anxiety related to injections
  - Patient satisfaction
  - The impact of the musical intervention on the medical procedure (botulinum toxin injections) as assessed by the physician at the end of the session

To evaluate the effect of exposure to a musical intervention session during Injection Visit 2, in order to assess the impact of repeated exposure to the musical intervention on:

- Injection-induced stress as assessed by HRV parameters excluding the LF/HF ratio
- Injection-induced pain
- Anxiety related to injections
- Patient satisfaction
- The impact of the musical intervention on the medical procedure (botulinum toxin injections) as assessed by the physician at the end of the session

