# STUDY POPULATION

## Inclusion Criteria

- Adult patients (male or female) with neurologically-originating spasticity (e.g., multiple sclerosis, stroke, traumatic brain injury) eligible for botulinum toxin injection treatments
- Patients known to experience pain and/or anxiety
- Ability to provide informed consent to participate in the research
- Affiliation with a social security system

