**V1 (Month 0): Injection visit 1 (inclusion visit)**
At this visit, informed consent will be obtained from the patient or their legal guardian. The physician will provide a copy of the signed consent form to the patient or their legal representative/trustee/designated person. The following data will be collected: age, sex, pathology, and date of first botulinum toxin injection. Once this information is recorded, randomization will be performed by the Clinical Research Associate (CRA) of the department.
For all injections, the same standardized protocol will be applied for each patient (ultrasound-guided or electromyography localization technique, MYOBOT needle [26G], analgesia by ice for palmar or plantar injections upon patient request) in an outpatient setting.

During the first injection visit, a Polar H10 heart rate monitor chest strap will be placed on the patient to measure stress induced by the medical procedure. A minimum recording period of 10 minutes is required prior to the injections to collect reliable baseline data. During this time, the physician will prepare the syringes for botulinum toxin injection. The patient will complete the self-administered anxiety questionnaire (STAI-Y1).

The control group (CT-IM) will not receive any specific intervention other than the Polar H10 heart rate monitor. This group will undergo botulinum toxin injections according to usual practice within the department, with the same evaluations as the intervention group (IM-IM).

The intervention group (IM-IM) will receive a tablet and headphones to listen to music during the botulinum toxin injections. Before the injection, during the waiting time, the patient, with or without assistance, will choose the music to listen to based on personal preferences. The music duration can be adjusted to fit the length of the medical procedure.

At the end of the injection session (both groups), a Visual Analog Scale (VAS) will be presented to the patient to rate pain on a scale from 0 to 10. The nurse or CRA will ask the patient to rate their satisfaction with the intervention using a VAS. Anxiety will be measured using the STAI-Y1 questionnaire. Time perception will also be evaluated based on patient self-report and compared to the actual duration of the medical procedure.

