**V2 (Month 3 ± 1 month): Injection visit 2**
At this visit, both groups will receive a tablet and headphones to listen to music during the botulinum toxin injections. The musical intervention, as described below, will begin immediately after the medical consultation and completion of the STAI-Y1 anxiety questionnaire. The CRA or nurse will set up the patient on the medical bed and place the Polar H10 chest strap. The patient, with or without assistance, will choose the preferred music. During a resting period of at least 10 minutes, the patient will listen to the selected music. The music duration can be adjusted to match the length of the medical procedure.

At the end of the injections (both groups), a Visual Analog Scale (0 to 10) will be used to assess perceived pain. The nurse or CRA will ask the patient to rate their satisfaction with the intervention via VAS. Anxiety will be quantified using the STAI-Y1 questionnaire. Time perception will again be assessed via self-report.

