## Product presentation

A pair of headphones and a tablet will be available for the entire duration of the study. The headphones will be placed on the patient’s ears once they are positioned on the examination table. The nurse assisting the physician during the botulinum toxin injections will help the patient select the music they wish to listen to. Additionally, the patient may navigate through the application to modify the music style or adjust the duration of the listening session, if desired. The objective is to ensure that the listening duration extends throughout the medical procedure, continuing until the completion of the injections. The listening session may also be controlled by the investigator or the nurse, who can stop the device at any time.

[figure not shown]

**Figure 3** : Application MUSIC CARE^®^

The MUSIC CARE® application is available for download on various platforms (AppleStore or PlayStore). The PMR department will have an account to allow patients to benefit from this therapeutic approach. The first image in Figure 2 shows the different session choices based on the patient’s preferences. In the context of the MUSIBOT study, the application will be used with the aim of reducing stress related to the medical procedure. A diagram is then presented to explain to the patient the "U-shaped" sequence. Once the patient selects the "pain" program, another page appears, allowing the patient to choose the music style they wish to listen to during the session. Music can be selected by category. The patient selects the music to listen to and is then asked to rate their current level of pain using a Visual Analog Scale (VAS). The music begins according to the "U-shaped" sequence, with a minimum duration of 20 minutes. The duration can be adjusted based on the length of the medical procedure. The patient/nurse controls the application and can modify settings as needed.

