# DATA COLLECTION

Data collected in the case report form will include the inclusion and exclusion criteria (see above), demographic data (age, sex), date of first injection, injected muscles, dose administered, and type of botulinum toxin used, clinical evaluation data, pain level measured by a visual analog scale (VAS), heart rate variability (HRV) parameters, anxiety measurements before and after injections, patient-reported perception of time (in minutes) during the procedure, actual duration of the medical procedure, patient satisfaction with the intervention, quality of the injection conditions as assessed by the physician immediately after the session, and any potential adverse events encountered.

Regarding heart rate variability data, the following parameters will be collected: Mean RR interval, Mean Heart Rate, SDNN (standard deviation of NN intervals), RMSSD (root mean square of successive differences), pNN50 (percentage of successive RR intervals differing by more than 50 ms), TINN (triangular interpolation of NN intervals), VLF (very low frequency), LF (low frequency), HF (high frequency), LF/HF ratio, SD1 and SD2.

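### Pain is rated for the study only after the injections, while at visit 1 the app asks the music arm alone about pain beforehand; one matched pre-injection rating would be a cheap improvement

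*Protocol*

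**What the plan says.** The secondary objectives (section 3.2) include "Injection-induced pain" at both injection visits. Section 6.1.2 defines the endpoint as pain intensity, "measured immediately after the injection session using a simple Numerical Rating Scale (NRS) ranging from 0" to 10.

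The visit descriptions in section 7.1 agree on the timing but name another instrument. At the end of visit 1 "a Visual Analog Scale (VAS) will be presented to the patient to rate pain on a scale from 0 to 10"; at the end of visit 2 "a Visual Analog Scale (0 to 10) will be used to assess perceived pain". Section 9 lists "pain level measured by a visual analog scale (VAS), heart rate variability (HRV) parameters, anxiety measurements before and after injections": anxiety has two time points, pain has none stated.

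Section 8.3 describes the app screens. After choosing a program and a music style, the patient "is then asked to rate their current level of pain using a Visual Analog Scale (VAS"), and the music then begins. Under section 7.1, controls at visit 1 receive only the heart rate belt, and their assessments are said to match those of the IM-IM group. At visit 2 both groups use the app.

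Eligibility (section 5.1) covers "Patients known to experience pain and/or anxiety".

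**The concern.** Two features of the pain measurement fit poorly with the rest of the design.

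First, the objective concerns pain caused by the injections, but the single rating cannot separate it from pain the patient already had. LF/HF and anxiety both have a value before the injections; pain does not. A later analysis plan cannot repair this, because a rating that was never taken cannot be recovered.

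Second, at visit 1, the only randomised comparison of music with no music, one arm is asked to score its pain shortly before the procedure and the other is not. This difference follows allocation, so randomisation does not remove it, and it conflicts with the statement that both arms have the same assessments.

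At stake are the precision and reading of the pain comparison at visit 1, and the interpretation of the visit 1 to visit 2 and within-group analyses of pain in section 10.4. Section 6.3 itself does not fully exclude a change in clinical status between the two injections.

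**Working it through.** **Pain questions by arm and visit** (sections 6.1.2, 7.1 and 8.3)

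| | IM-IM, visit 1 | CT-IM, visit 1 | Both arms, visit 2 |
|---|---|---|---|
| App asks current pain before the music | yes | no | yes |
| Pre-injection pain listed as study data | no | no | no |
| Pain rated after the injections | yes | yes | yes |

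The arms differ in one cell only: the app prompt at visit 1. It follows that within CT-IM the change from visit 1 to visit 2 coincides with the first appearance of the prompt as well as of the music.

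**The protocol's own figure.** No sample size or power is stated for pain. The only figure, 35 per group, concerns LF/HF (section 10.1: difference 1.8, SD 2.3, two-sided 5%, power 90%). It reproduces:

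n = 2 × (1.960 + 1.282)² × 2.3² / 1.8² = 34.3, rounded up to 35.

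Nothing in the pain point enters this calculation.

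**What a pre-injection rating could gain.** Let r be the correlation between pre- and post-injection pain within arms. The documents do not give it, so the values below are assumptions. Adjusting for the pre-rating multiplies the residual variance by 1 − r². This equals a sample size factor of 1/(1 − r²) and multiplies the detectable standardised difference by √(1 − r²). The post-only starting point is 0.634 SD, from a two-sample t-test with the planned 40 per group, two-sided 5% and an assumed 80% power.

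| Assumed r | Variance removed, r² | Sample size factor | Detectable difference (SD) |
|---|---|---|---|
| 0.1 | 1% | 1/0.99 = 1.01 | 0.634 × 0.995 = 0.63 |
| 0.3 | 9% | 1/0.91 = 1.10 | 0.634 × 0.954 = 0.60 |
| 0.5 | 25% | 1/0.75 = 1.33 | 0.634 × 0.866 = 0.55 |
| 0.6 | 36% | 1/0.64 = 1.56 | 0.634 × 0.800 = 0.51 |

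**Covariate, not change score.** A simple difference has variance factor 2(1 − r), which exceeds 1 whenever r is below 0.5. At r = 0.3 the detectable difference would worsen to 0.634 × √1.4 = 0.75; at r = 0.5 it would stay at 0.63. The pre-rating should therefore be a covariate and not be subtracted.

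**The one-arm prompt.** No calculation is possible. The documents contain nothing from which the size or sign of its effect could be derived.

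**The case against.** The strongest case on the other side is that a rating straight after the procedure is a deliberate and common way to measure procedural pain. Section 10.4 speaks of variation for stress and anxiety but simply of pain, so the plan may intend an intensity endpoint and not a change. The rationale in section 2.1 locates the pain mainly in skin puncture, localisation technique and injection site. If resting pain is near zero in most patients, a pre-rating would correlate weakly with the endpoint and gain almost nothing, as the first row of the precision table shows. The app prompt can also be seen as part of the delivered intervention, and asking everyone would extend any effect of a prompt to controls who are meant to follow usual practice.

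Much of this stands, and it rules out several stronger readings that a reader might infer:

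- *That patients are selected for background pain.* The criterion can be met through anxiety alone, and it does not say whether the pain is at rest or procedural.
- *That the visit 1 pain contrast is biased by the missing baseline.* Randomisation balances pre-existing pain in expectation.
- *That the prompt hides or inflates a music effect, for example by anchoring on the same scale.* The documents give no direction, and section 8.3 gives no range for the app's scale.
- *That the arms differ in this way throughout.* At visit 2 both use the app.

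What the objection does not remove is the mismatch between section 8.3 and the promise of equal assessments in section 7.1, or the fact that pain already present cannot be separated from injection pain in the score. If the prompt is meant as part of the intervention, the protocol does not say so.

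**Conclusion.** The point holds as a cheap improvement to a secondary endpoint. At visit 1 there is an arm-dependent difference in how often pain is asked about, and it conflicts with the stated equality of assessments. The lack of a common pre-injection rating costs precision and interpretability, including for the between-visit and within-group analyses, but does not bias the randomised visit 1 comparison.

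The precision gain lies between 1% and 36% of residual variance for r between 0.1 and 0.6. That range is entirely assumed, and the gain may be negligible if pain is mainly procedural. The effect of the prompt is unknown in both size and direction.

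Section 10.2 declares the secondary analyses exploratory. The primary endpoint, its analysis and the 35 or 40 per group are untouched.

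**What to change.** 1. Ask every patient in both arms, at both visits, one identical current-pain question on the endpoint's scale. Place it with the pre-injection STAI-Y1, before any music.
2. Adjust the post-injection pain comparison for this rating as a covariate.
3. Skip the in-app pain prompt in the trial, or have controls answer the same prompt at the same moment at visit 1. Align section 7.1 with whichever is chosen.
4. Name one pain instrument. Section 6.1.2 says NRS; sections 7.1 and 9 say VAS. Pre- and post-injection ratings need the same scale.

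The cost is one question per visit, one CRF field and one covariate, with no added enrolment. There are two downsides. Controls would also be asked about pain before the injections, a small departure from usual practice but the same in both arms. Patients already enrolled would lack the value; they can stay in the analysis with a missing-baseline indicator.

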**Abstract**

**Context**

Botulinum toxin injections are a common treatment for managing spasticity resulting from central nervous system damage, including stroke, multiple sclerosis, and traumatic brain injury. However, the injections are associated with perceived pain, and many patients experience significant anticipatory stress regarding future sessions. The intensity of this stress varies among individuals.

Music therapy, particularly receptive musical interventions structured around a U-shaped sequence, promotes progressive relaxation through distinct musical phases. This method has demonstrated efficacy in reducing pain and anxiety across various clinical contexts, including chronic and acute pain, Alzheimer’s disease, fibromyalgia, and neurologically mediated pain. Given the painful nature of botulinum toxin injections, this study proposes the use of receptive music therapy to improve patient tolerance of the procedure. We hypothesize that receptive musical intervention can reduce injection-induced stress in adults undergoing botulinum toxin treatment. To our knowledge, no studies have specifically investigated the effect of music therapy on stress related to botulinum toxin injections.

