## 6.3 Measures to minimize and avoid bias

Randomization will be performed using randomly sized blocks.
The primary objective of this study is to evaluate the effect of exposure to a musical intervention session during botulinum toxin injections on the stress induced by the injection. More specifically, this objective will be assessed at the first injection visit (Injection Visit 1).

As this is a waiting-list randomized study, patients who do not receive the musical intervention at Injection Visit 1 will be offered the intervention during the subsequent injection visit (Injection Visit 2). This design aims to improve acceptability of participation (acceptance of randomization compared to a standard parallel-group randomized trial), thereby enhancing study feasibility.

The comparison at Injection Visit 2 is a secondary objective, intended in particular to measure the effect of repeated exposure to the musical intervention and intra-individual variability before and after the intervention (assessed via mixed models for secondary endpoints; see section 10.4).

A crossover experimental design was considered but ultimately rejected, given that heart rate variability results could be influenced in patients receiving usual care at Injection Visit 2 after having undergone the musical intervention at Injection Visit 1. Furthermore, although it is unlikely that patients’ clinical status would change significantly between two injections, this possibility cannot be entirely excluded, representing a potential major bias (risk of carryover effect) for a crossover study. Finally, loss to follow-up or study discontinuation would have a greater impact on a crossover design compared to the proposed waiting-list design, where the primary objective is assessed at Injection Visit 1.

A strictly anonymous list of patients who decline to participate in the study will be maintained to report inclusions in the flowchart and to analyze the representativeness of the patient sample included in the study.

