## Secondary analyses

The main analysis may be supplemented by a multivariate analysis using multiple linear regression to account for covariates selected based on univariate analysis results and their clinical relevance (including sex and age of the patients). Special attention will be given to the study of multicollinearity (Farrar and Glauber test and VIF indicator). The validity of the model (normality of residuals and homogeneity of variances) will be visually assessed. The results will be expressed in terms of regression coefficients, effect sizes, and 95% confidence intervals.

Subgroup analyses will be conducted for the primary endpoint, based on the sex and age of the patients. The interaction between group and subgroup will be explored. The results will be expressed in terms of regression coefficients, effect sizes, and 95% confidence intervals.

Analyses aimed at studying the effect of exposure to a music intervention session during botulinum toxin injections at visit #1, in terms of stress induced by the injection for HRV parameters other than LF/HF, pain induced by the injection, anxiety during the injections, patient satisfaction, and the effect of music intervention on the medical procedure (botulinum toxin injections) as expressed by the physician at the end of the session, will follow the same statistical analysis plan as for the primary endpoint.

Analyses to study the effect of exposure to a music intervention session at visit #2 (to evaluate the effect of repeated exposure to a music intervention) on the variation of stress, pain, variation of anxiety, patient satisfaction, and the effect of music intervention on the medical procedure (botulinum toxin injections) as expressed by the physician at the end of the session, will rely on mixed models.

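### At visit 2, anxiety is analysed only as a within-visit STAI-Y1 change, so any carry-over from visit 1 music that lowers arrival anxiety is subtracted from the repeated-exposure comparison

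*Protocol*

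**What the plan says.** **Objective.** Section 3.2 sets the visit 2 evaluation "in order to assess the impact of repeated exposure to the musical intervention on" stress, pain, anxiety, satisfaction and injection conditions. Section 6.3 describes the visit 2 comparison as "intended in particular to measure the effect of repeated exposure to the musical intervention". Both arms receive music at visit 2, so the randomised contrast of IM-IM with CT-IM isolates what the earlier session adds.

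**Endpoint.** Section 6.1.2 gives anxiety as "Anxiety variation measured by the self-administered State-Trait Anxiety Inventory - Form Y, State subscale (STAI-Y1) during Injection Visits #1 and #2, before and after" the injections. Section 10.4 applies mixed models at visit 2 to effects "on the variation of stress, pain, variation of anxiety, patient satisfaction" and the physician's appraisal. No listed endpoint or analysis uses the visit 2 STAI-Y1 level by itself.

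**Timing.** Section 7.1 puts visit 2 at month 3, plus or minus one month. The visit 2 music starts only once the STAI-Y1 has been completed.

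**Background.** The abstract states that "many patients experience significant anticipatory stress regarding future sessions".

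**The concern.** The visit 2 starting score is not a neutral baseline. It is measured after the randomised exposure whose lasting effect is being sought, and before any new exposure. If one music session makes patients less apprehensive about the next, that shows first as a lower arrival score in IM-IM. A before-to-after change then treats the benefit as less room to fall.

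At stake is the conclusion on repeated exposure for anxiety. The trial could report no effect, or an apparent disadvantage for IM-IM, while IM-IM patients are less anxious both before and after the injections.

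**Working it through.** **The plan's own figure.** The only sizing figure, in section 10.1, concerns the visit 1 LF/HF change: a difference of 1.8, SD 2.3, two-sided 5%, power 90%. The normal formula gives n = 2 × (1.960 + 1.2816)² × 2.3² / 1.8² = 34.3, so 35 per group, as stated. The present point does not depend on it. The protocol gives no carry-over size for anxiety.

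**Scale.** Section 6.1.2 gives 20 items scored 1 to 4, so the total runs from 20 to 80.

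**Algebra.** Let visit 1 music lower the visit 2 arrival score in IM-IM by c, and let a share k of that be present after the injections. For IM-IM minus CT-IM, where negative means less anxiety in IM-IM:

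- pre-injection level: −c
- post-injection level: −kc
- within-visit change: −kc − (−c) = c(1−k)

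With c and k assumed:

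| c | k | before | after | change |
|---|---|---|---|---|
| 5 | 1.2 | −5 | −6 | −1 |
| 5 | 1 | −5 | −5 | 0 |
| 5 | 0.8 | −5 | −4 | +1 |
| 5 | 0.5 | −5 | −2.5 | +2.5 |
| 5 | 0 | −5 | 0 | +5 |
| 2 | 0.5 | −2 | −1 | +1 |

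The contrast in change is zero when the arrival benefit persists in full. It has the wrong sign when part of that benefit fades during the session. It shows only the excess when the later benefit is larger. An effect on reactivity alone (no arrival shift) stays fully in the change score.

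**Does adjusting for the visit 1 change help?** It does not. A simulation with 200,000 per arm used SD 10 and correlations of 0.8 within a visit, 0.6 between the same time point at the two visits, and 0.5 otherwise. The slope of the visit 2 change on the visit 1 change is then (0.6 − 0.5 − 0.5 + 0.6) / (2 − 1.6) = 0.5. With c = 5, k = 0.5 and an assumed 5-point music effect at visit 1, the contrast moves from +2.5 to 2.5 + 0.5 × 5 = +5.0 (simulated 4.99), because the visit 1 change is itself affected by treatment. The model in section 10.4 is fitted to the same change scores with visit 1 as reference, so it does not restore the arrival difference either.

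**Do levels recover it?** In the same simulation, unadjusted visit 2 contrasts were −4.97 before and −4.98 after for k = 1, and −5.00 and −2.54 for k = 0.5. Adjusting for a clean visit 1 pre-injection score gave −4.98 and −4.99, and −5.00 and −2.54. This only confirms the algebra. It is no evidence that carry-over exists.

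**The case against.** The strongest reply is that a before-to-after change is the natural measure of what the injections provoke, and that it keeps the same form at both visits. Section 6.3 also gives the visit 2 comparison a second purpose, within-patient variability. This stands: the change remains a valid randomised comparison of reactivity. It does not settle the point for anxiety, because section 3.2 words stress and pain as injection-induced but anxiety more broadly, as relating to the injections. Anxiety on arrival falls within that wording.

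Three stronger readings are tempting but not supported.

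- *That the stress endpoint fails in the same way.* That endpoint is "Patient stress during Injection Visit #2, estimated by changes in HRV, measured before and during the botulinum toxin injection session using the LF/HF ratio", and its objective is worded as injection-induced, which a change measures. Under section 7.1, music also plays in both arms during the visit 2 rest period, so the LF/HF starting value need not reflect arrival state.
- *That the protocol concedes carry-over into arrival anxiety.* Section 6.3 says that HRV "results could be influenced in patients receiving usual care at Injection Visit 2 after having undergone the musical intervention at Injection Visit 1". That describes the rejected crossover sequence, concerns HRV and not STAI-Y1, and does not say that the starting value would shift. It shows only that the authors thought an effect lasting to visit 2 possible.
- *That the change should be replaced by levels adjusted for visit 1.* Levels alone mix arrival state with reaction to the injections. Section 7.1 also describes randomisation before the visit 1 STAI-Y1, so that score is not clearly free of knowledge of the allocation.

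It is also fair to say that a benefit lasting 2 to 4 months after one session is unproven, and that these comparisons are exploratory (section 10.2).

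**Conclusion.** The point holds for anxiety, in conditional form. The repeated-exposure comparison rests only on a change score whose starting value comes after the randomised exposure, so any carry-over that lowers arrival STAI-Y1 in IM-IM is subtracted. The distortion equals c, the whole arrival shift. With an assumed c of 5 points, the change contrast runs from −1 (k = 1.2) through 0 (k = 1) to +5 (k = 0). Both c and k are assumptions, and if c is zero nothing is lost.

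A reader might infer that the trial will report the wrong sign; the documents give no basis for predicting that. The visit 1 primary endpoint and the sample size are untouched. Visit 2 pain, satisfaction and injection conditions are single post-session scores and are unaffected.

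**What to change.** In sections 6.1.2 and 10.4:

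1. For the repeated-exposure objective, add two visit 2 anxiety outcomes compared between arms: the pre-injection STAI-Y1 level and the post-injection STAI-Y1 level. Do not adjust either for the visit 2 pre-injection score.
2. Adjust for the visit 1 pre-injection STAI-Y1 only if it is completed before the allocation is known. Otherwise compare without that adjustment; the unadjusted randomised comparison is valid.
3. Keep the within-visit STAI-Y1 change as a separate measure of reactivity to the injections, and state that it is not to be read alone as the effect of repeated exposure.
4. Leave the LF/HF change as the measure of injection-induced stress, with the same caution in interpretation.

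Section 9 already collects anxiety before and after the injections, so no visit, patient or questionnaire is added. The cost is one or two more exploratory comparisons, and a visit 2 anxiety outcome that differs in form from the one at visit 1.
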